### Secondary outcomes

*Health-related aspects* are measured from three perspectives: sense of coherence, experience of control, and quality of life. *Sense of coherence* is measured with the Sense of Coherence (SOC) [31] tool, a self-rating questionnaire of 13 items that indicates how well an individual copes with stress and stays healthy. Items are rated on a seven-step numeric Likert scale from 1 (very often) to 7 (very seldom or never). The Swedish 13-item SOC used here is a common measurement that has demonstrated good test-retest reliability and internal consistency [32].

*Experience of control* is measured with the Mastery Scale [33]. This self-rating questionnaire comprises seven items and indicates the extent to which an individual experiences control and mastery of situations that influence his or her everyday life. Items are rated on a four-step categorical Likert scale from 1 (completely agree) to 4 (do not agree at all). This questionnaire has been found to have good internal consistency and construct validity [34].

*Quality of life* is measured with the Manchester Short Assessment of quality of life (MANSA) [35], an interview-based questionnaire of 12 items, including the individual’s general rating of life satisfaction and his or her satisfaction with work, finances, social relationships, leisure, housing situation, family relationships, and both physical and mental health. Items are rated on a seven-step numerical Likert scale from one to seven, with higher scoring reflecting greater satisfaction. The Swedish version used here has been found reliable in terms of internal consistency and construct validity [36].

*Intervention-related aspects* are measured by two factors: therapeutic alliance and patient satisfaction. *Therapeutic relationship* was measured using the Helping Alliance Questionnaire (HAq-II) [37], which indicates the strength of the alliance between patient and therapist. There is both a patient version and a therapist version, allowing each to independently rate the therapeutic alliance. The HAq-II consists of 19 items scored on a six-step categorical Likert scale from 1 (strongly disagree) to 6 (strongly agree). The questionnaire has been found internally consistent and reliable for test-retest purposes [37], and it demonstrates good convergent validity [37, 38].

*Patient satisfaction* is measured with the Client Satisfaction Questionnaire (CSQ) [39], which indicates the patient’s satisfaction with the received intervention. The eight-item instrument uses a four-step categorical Likert scale from 1 (very dissatisfied) to 4 (very satisfied), and it has been found to have good internal consistency [40] and construct validity [41, 42].

### Sample size/power calculation and randomization

The power calculation indicates that 60 patients would be needed in each group to obtain an effect size of 3.6 (scale on 9–63) for the outcome variable Satisfaction with Daily Occupations (SDO), with 80 % power (*p* = 0.05). To compensate for possible losses, a total of 130 patients will be recruited. After granting informed consent, patients are allocated (by means of sealed envelopes prepared by a researcher not involved in the study) to either intervention or treatment as usual. In all, 65 patients will be randomized to the TTM (intervention group) and 65 to treatment as usual (control group).

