*Satisfaction with everyday activities* is measured with the tool Satisfaction with Daily Occupations (SDO) [9], a semi-structured interview focusing on perceived satisfaction with everyday activities in work, leisure, domestic tasks, and self-care. The individual first indicates whether he or she presently performs an activity and then rates his or her satisfaction with that performance on a seven-step numeric Likert scale from 1 (worst possible) to 7 (best possible). The original version has nine items and has demonstrated satisfactory internal consistency, construct validity [27, 28], and test-retest reliability [28]. The present study used a 14-item version in order to cover more activities in the areas of leisure, domestic tasks, and self-care; this version has also shown satisfactory internal consistency [29].

*Balance in everyday life activities* is measured with the Occupational Balance Questionnaire (OBQ) [30], a 13-item self-rating questionnaire that indicates an individual’s perception of balance. Balance is rated on a six-step categorical Likert scale, from 0 (completely disagree) to 5 (completely agree). The OBQ has shown good internal consistency and test-retest reliability [30].

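### The only power calculation uses the nine-item SDO range (9–63), but the trial collects a 14-item SDO, so the stated 80% power is not tied to the score collected

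*Protocol article*

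**What the plan says.** In the protocol article, Sample size/power calculation and randomization, the calculation states that a sample of 60 "would be needed in each group to obtain an effect size of 3.6 (scale on 9–63) for the outcome variable" in question, which is the SDO, at 80% power and p = 0.05. Recruitment is raised to 130 (65 per group) to cover losses. The SDO is the only outcome this section names, and no SD is stated.

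The Primary outcomes section describes the SDO as items rated from 1 to 7. It says "The original version has nine items" and then: "The present study used a 14-item version in order to cover more activities". It adds that the longer version has also shown acceptable internal consistency. It does not say how the items are combined into a score.

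**The concern.** Nine items rated 1–7 sum to exactly 9–63, so the power sentence describes the original instrument. Fourteen such items sum to 14–98. The article does not say that a nine-item subscore will be analysed, that the 14-item total will be rescaled to 9–63, or that 3.6 was converted from one version to the other.

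Two things depend on this. First, it is the trial's only sample-size justification. A longer sum score has a larger SD, so the same 3.6 points is a smaller standardised difference on it, and the 80% does not carry over automatically. Second, 3.6 points is the only benchmark in the article for judging an SDO difference, and a reader cannot tell which score it belongs to. If the choice between the two scores stays open until results are known, it becomes a choice made after seeing the data.

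**Working it through.** **Inputs from the article.** n = 60 per group; difference 3.6; scale 9–63; 80% power; p = 0.05; items rated 1–7; nine items originally, 14 in this trial; 1:1 allocation.

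**Assumptions, because the article is silent.** Two-sided test; two-sample comparison of means (the planned analysis is non-parametric, see the last step); items summed; equal item variances and one common inter-item correlation ρ across all items.

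**Step 1: scale ranges.** 9 × 1 to 9 × 7 = 9–63, which matches the power sentence. 14 × 1 to 14 × 7 = 14–98, which does not.

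**Step 2: the plan's own figure.** With no SD, 60 per group can only be solved backwards. By the normal approximation, SD = 3.6 × √(60/2) / (1.960 + 0.842) = 3.6 × 5.477 / 2.802 = 7.04. By the noncentral t, the standardised difference is 0.516, so SD = 3.6/0.516 = 6.98. Going forwards with SD 7.0, the normal approximation returns 60 per group and 80.4% power. The figure 3.6 must be raw points: a standardised difference of 3.6 would need only 2 per group. The 60 is therefore attainable on 9–63, though it cannot be confirmed independently. The move from 60 to 65 per group is a 5/65 = 7.7% allowance for losses and is coherent.

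**Step 3: SD of the 14-item sum.** The variance of a k-item sum is proportional to k[1 + (k − 1)ρ], so

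SD14 = 6.98 × √{14(1 + 13ρ) / [9(1 + 8ρ)]}.

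For the lower end of ρ, I take acceptable internal consistency to mean Cronbach's alpha of about 0.7 (an assumption). With 14 items, alpha = 14ρ/(1 + 13ρ), and ρ = 0.14 gives 1.96/2.82 = 0.70. Then SD14 = 6.98 × √(39.48/19.08) = 6.98 × 1.4385 = 10.04. The upper end, ρ = 1, is the same as scaling by range: 84/54 = 14/9 = 1.556, so SD14 = 10.86.

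**Step 4: power with 60 per group (noncentral t, two-sided 0.05).** The proportional target is 3.6 × 14/9 = 5.6 points.

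| ρ | SD14 | Power, 3.6 points kept | Power, 5.6 points | Detectable at 80% power (0.516 × SD14) |
|---|---|---|---|---|
| 0.14 | 10.04 | 49.5% | 85.8% | 5.18 |
| 0.3 | 10.45 | 46.5% | 82.9% | 5.39 |
| 1 | 10.86 | 43.7% | 80.0% | 5.60 |

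**Step 5: sensitivity.** Allowing for a rank test with efficiency 0.955 changes the back-solved SD from 7.04 to 6.88. A one-sided test would make it 7.93. Neither affects the mismatch in Step 1.

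**The case against.** The strongest reply is that the article never claims 80% power for 3.6 points on a 14-item score: it attaches 3.6 to 9–63 explicitly. The low power figures appear only when a reader carries the raw 3.6 across unchanged. This stands. A reader might infer that the trial has roughly even odds of missing its target effect; the article does not support that, because a proportional target leaves power at 80% or more with the same 60 per group.

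A second reply is that the 14-item form is an expansion of the same instrument, that the article gives no scoring rule, and that such rules often sit in a full protocol or analysis plan not shown here. If the nine original items are contained in the longer form and scored separately, the calculation applies as it is. This stands as a possibility, but the article does not say it. A missing scoring rule would not be a finding in itself. Here, though, the article states a scale, and that scale disagrees with its own description of the outcome.

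A third reply is that no calculation error has been shown. That is correct: 60 per group follows from an SD of about 7.0, and the fault is an internal inconsistency.

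It would also be tempting to widen the range by treating the items as uncorrelated (ρ = 0: power 61% for 3.6 points, detectable difference 4.5). That implies an alpha of zero, contrary to what the article reports for the 14-item version, so I have not used it.

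**Conclusion.** The power statement is wrong as written. It quotes the range of a nine-item score, while the trial collects 14 items and gives no link between them. That conclusion needs only the item arithmetic and sum scoring, which the 9–63 range itself supports.

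The size of the consequence is conditional. It rests on a back-solved nine-item SD of about 7.0, a common inter-item correlation of about 0.14 or more, and added items that behave like the original nine. On that basis, the same 60 per group means about 44–50% power for an unchanged 3.6 points or about 80–86% for 5.6 points. Which applies depends on a scoring and target decision the article does not record. The trial is not shown to be underpowered, and nothing here calls for a different sample size.

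**What to change.** Before unblinded analysis, reconcile the two sections in one of two ways.

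1. **Nine-item score.** If the original nine items are contained in the 14-item form, name their sum (9–63) as the powered SDO score, so that the existing calculation applies, and report the 14-item total as supportive.
2. **14-item score.** Keep the 14-item score and restate the calculation on its own scale: the SD used and its source, a target difference justified on that scale (or the explicit conversion from 3.6), and the power that 60 per group then gives. The target should not simply be read off from what 60 per group can detect.

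In either case, state the scoring rule and the SD. The cost is a corrected sentence and a scoring rule, with no extra patients. The downside of the second option is a larger stated detectable difference in points, about 5.2–5.6 on 14–98 under the assumptions above.

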### Statistical analysis

At the study’s completion, data analysis will be performed on the principle of intention to treat [15]; in other words, outcomes will be analysed using the basis of all participants. Missing data for dropouts will be estimated using the last data obtained before a participant dropped out. Descriptive and analytic statistics will be used to compare the outcomes between the intervention group and the control group at baseline, after intervention, and at 3- and 12-month follow-ups. As all variables will be assessed on either a nominal or an ordinal scale, statistical analysis with non-parametric methods will be used.

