### Context and procedure

This study is being conducted at primary health-care centres and general outpatient mental-health-care units in three counties in the south of Sweden. Thirteen occupational therapists specifically trained in the TTM intervention ask patients who meet the inclusion criteria to participate and obtain informed consent from those who agree. In order to assess the therapeutic alliance, the occupational therapist does not meet a patient more than twice before asking him or her to participate in the study. Patients who do not wish to participate in the study receive the usual treatment. After recruiting, each patient is allocated to either the TTM or the control group (occupational therapy as usual). Drug treatment continues as prescribed, and dropouts are documented during the study. The same occupational therapists perform both TTM intervention and treatment as usual. In order to ensure that the occupational therapists actually deliver two different treatments they complete fidelity forms after each session.

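### Last observation carried forward is the only stated handling of dropouts and can bias every post-baseline comparison, in either direction, if scores change after the last visit or dropout differs by arm

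*Protocol article*

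**What the plan says.** The Statistical analysis section of the protocol article commits to intention to treat, so that "outcomes will be analysed using the basis of all participants". For those who leave it states: "Missing data for dropouts will be estimated using the last data obtained before a participant dropped out". That is single-value last observation carried forward (LOCF). The groups are compared "at baseline, after intervention, and at 3- and 12-month follow-ups", and "statistical analysis with non-parametric methods will be used". No other treatment of missing data is given, so this rule serves every outcome at all three post-baseline visits.

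The section on sample size and randomization asks for 60 patients per group to detect 3.6 points on the SDO (scale 9–63) with 80% power at 0.05. It then adds a margin: "To compensate for possible losses, a total of 130 patients will be recruited", that is 65 per arm. It gives no SD, no expected dropout rate and no time point for the power.

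**The concern.** There are only four assessments: one before treatment, one directly after it, and two in follow-up. Someone lost before the second has nothing but a pre-treatment score to carry, and that score stands in for the result 12 months after completion. The Background section reports that an earlier group of TTM patients improved after the intervention, so a carried baseline is a poor substitute for a later score. The control arm also receives five one-hour sessions, so change in both arms is plausible.

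If dropout is equal, carried baseline values shrink a real difference. If it is unequal, the arm that loses more patients looks worse than it is, which can create, inflate or hide a difference. LOCF is therefore not reliably conservative.

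The rule also sits awkwardly beside the sample size. The margin from 120 to 130 is reasoned as if lost patients leave the analysis, while the analysis rule keeps all 130 in, some with a possibly diluted effect.

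**Working it through.** **Inputs from the article.** Difference 3.6; 60 per group; 80% power; alpha 0.05 (two-sided assumed); 65 per arm recruited.

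**Assumptions not in the article.** The SD, the dropout rates, a 7-point improvement in both arms, and dropout unrelated to outcome.

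**1. The plan's own figure.** No SD is stated, so 60 per group cannot be checked independently; it can only be solved backwards. SD = 3.6 / [(1.960 + 0.842) × √(2/60)] = 7.04. SD 7.0 returns n = 60 per group with 80.4% power. A one-sided test would imply an SD of about 7.93. SD 7 is used below. The step from 60 to 65 implies a loss of 1 − 60/65 = 7.7%.

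**2. Dilution with equal dropout.** Let d be the dropout share and f the share of the effect already present in the carried value. The expected difference is 3.6 × [(1 − d) + d·f], and the standard error with 65 per arm is 7 × √(2/65) = 1.228. Normal-approximation power:

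| d | f = 0 (baseline carried) | f = 0.5 | f = 1 | Dropouts left out |
|---|---|---|---|---|
| 7.7% | 3.32; 77.2% | 3.46; 80.5% | 3.60; 83.4% | 80.4% |
| 20% | 2.88; 65.0% | 3.24; 75.1% | 3.60; 83.4% | 74.6% |

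(With the t distribution, the last entry is 74.0%.) The break-even against leaving dropouts out is (1 − d) + d·f = √(1 − d). At d = 0.0769 this gives f = (0.9608 − 0.9231)/0.0769 = 0.49. The margin for losses therefore survives if carried values hold about half the effect or more.

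**3. Unequal dropout, baseline carried.** With improvement 7 in control and 7 + δ in TTM, the expected LOCF difference is (1 − d_T)(7 + δ) − (1 − d_C)·7.
- δ = 0, 10% TTM vs 25% control: 7 × (0.25 − 0.10) = 1.05.
- δ = 3.6, 10% vs 25%: 0.90 × 10.6 − 0.75 × 7 = 4.29.
- δ = 3.6, 25% vs 10%: 0.75 × 10.6 − 0.90 × 7 = 1.65.

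**4. Simulation check.** Mann–Whitney test, 65 per arm, 3,000 runs per setting.
- Baseline carried, no true effect, 10% vs 25%: mean difference 1.05, type I error 12.2%.
- Baseline carried, true 3.6, equal 20%: mean 2.86, coverage of the true difference 91.3%. Rejection is 55.0%, against 70.8% with dropouts left out. This is below the 65% in step 2 because mixing improved and unimproved scores also widens the spread, which the formula holds at 7.
- Baseline carried, true 3.6, 25% vs 10%: mean 1.60, coverage 69.5%.
- Post-intervention value carried and scores level afterwards: mean 3.61 to 3.62 in every dropout pattern with a true 3.6, and type I error 4.8% to 5.8%.

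**5. Standard errors.** With baseline carried, true 3.6 and equal 20% dropout, the average nominal standard error was 1.378 and the actual spread of the estimate 1.392. With 25% vs 10% they were 1.374 and 1.366. The standard error is right for what LOCF estimates; coverage falls because the estimate is biased.

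**The case against.** The strongest reply is that the harm is conditional. If patients leave after the post-intervention visit and scores then hold, LOCF shows no bias and even retains more power than leaving dropouts out. The Background section cites a 3-year follow-up in which gains lasted, although it describes TTM patients only and says nothing about the control arm. Both arms have the same number, length and period of sessions with the same therapists, so the article gives no specific reason to expect a large imbalance in dropout. At the implied loss, with equal dropout, the worst case in the formula is 77% power rather than 80%. All of this stands. It limits the size of the problem but does not justify a rule that is safe only under a dropout pattern nobody can know beforehand.

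A reader might infer three stronger points that the article does not support:
- That LOCF makes the standard errors too small. Step 5 contradicts this under the assumptions used.
- That LOCF cancels the allowance for losses or contradicts the sample size. The two sections are not aligned, but the margin is lost only if carried values hold less than about half the effect.
- That the lack of sensitivity analyses is itself a defect. A statistical analysis plan may supply them. The article also does not call LOCF primary; it is simply the only method named.

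**Conclusion.** The point holds in conditional form. The article fixes single-value LOCF as its only stated dropout rule for all post-baseline comparisons, and following it as written can bias them in either direction. With baseline carried, a true 3.6 falls to about 3.3 (77% power) at 7.7% loss and to about 2.9 (65% power by formula, lower in simulation) at 20% loss. A 10% versus 25% imbalance with no true effect gives about 1 point of false difference and about 12% type I error. With losses only after the post-intervention visit and level scores thereafter, the bias is close to nil.

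These figures are illustrations. The SD, dropout rates and course of scores are assumed. The 9–63 range belongs to nine items scored 1 to 7, whereas the Primary outcomes section says the trial uses a 14-item SDO, so the point values do not transfer directly to that instrument. The comparison with observed data alone also assumes dropout unrelated to outcome.

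**What to change.** Replace LOCF in the main analysis with multiple imputation, done within arm and using baseline variables and all earlier scores. This keeps the planned non-parametric tests. State how the rank results will be combined across imputations, for example by pooling the Mann–Whitney probability with its standard error. If the analysis family may change, a likelihood-based repeated-measures model (ordinal or mixed) on all observed visits is an alternative, but it departs from the non-parametric choice and is more than a wording change.

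Add a delta-adjusted sensitivity analysis that shifts the imputed values by arm over a stated range, and keep LOCF at most as one further sensitivity analysis. In the sample-size section, state the dropout rate assumed and that the allowance refers to the revised analysis.

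The cost is a little more analysis work, with no added assessments. Analysis is planned for study completion, so the rule can be changed before the data are analysed. The downside is reliance on a missing-at-random assumption, which the delta-adjusted analysis is there to test.

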### Data collection

Data collection for this study is being carried out by project assistants on four occasions: 1 to 2 weeks before intervention, immediately after intervention, 3 months after completion, and 12 months after completion. Sociodemographic variables—namely, gender, age, diagnosis, accommodation, social networks, level of education, and employment—are documented. In addition, physical activity and health-care consumption (number of visits to service providers in the preceding month), inpatient care, pharmacological treatment (for insomnia, depression, or anxiety), and pharmacological-treatment compliance are recorded, along with any other health-care consumption. The data collection is blinded, i.e. the project assistants are unaware of treatment assignment.

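### Non-parametric comparisons rest on a premise untrue of several variables, and as described they leave baseline out of the follow-up comparison and plan no effect estimate in points

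*Protocol article*

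**What the plan says.** Protocol article, Statistical analysis: the choice of method and its only stated reason are "As all variables will be assessed on either a nominal or an ordinal scale, statistical analysis with non-parametric methods will be used". The comparison is described as using descriptive and analytic statistics to "compare the outcomes between the intervention group and the control group at baseline, after intervention, and at 3- and 12-month follow-ups". Baseline appears there only as one of four occasions. No covariate, change score or longitudinal model is named.

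Data collection: all participants are assessed one to two weeks before treatment, so a baseline value of the outcome scores is available. Age is recorded, and so is health-care use as the "number of visits to service providers in the preceding month".

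Primary outcomes: the Global Symptom Index is calculated from a 90-item checklist. SDO (14 items) and the Occupational Balance Questionnaire (13 items) are also multi-item instruments.

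Sample size/power calculation and randomization: the requirement is given as "60 patients would be needed in each group to obtain an effect size of 3.6 (scale on 9–63". It refers to SDO, and the calculation takes 80% power and a significance level of 0.05. No SD is given. Recruitment is 65 per group.

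**The concern.** There are three linked problems.

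1. The stated reason is wrong on the protocol's own variables. Age is a ratio variable and number of visits is a count. An index or sum over 9 to 90 items is not a single ordinal category, even though each item is ordinal.
2. The sample size gives point differences on SDO a meaning, because it targets 3.6 of them. The analysis section then treats the same score as one on which only order counts, and it plans no estimate to set against that target.
3. Baseline is compared between groups but, as described, is not used in comparing follow-up scores.

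At stake is precision that has already been paid for, and a result that can be read against the trial's own target. With about 60 per group, the outcome score at baseline is likely to be among the strongest predictors of the same score at follow-up.

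**Working it through.** **Inputs from the protocol article:** 60 per group, difference 3.6 on a 9–63 scale, 80% power, alpha 0.05. **Assumed:** two-sided test, normal scores, and baseline–follow-up correlation ρ of 0.3, 0.5 or 0.7. None of these is stated.

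**Step 1: reproduce 60 per group.** If 3.6 were a standardised effect, n = 2(1.960 + 0.842)²/3.6² = 1.2, which rounds up to 2 per group. So 3.6 must be raw points. The SD is missing, so 60 can only be solved backwards:

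SD = 3.6 / [(1.960 + 0.842) × √(2/60)] = 3.6 / (2.802 × 0.1826) = 7.04.

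A t-based calculation gives 6.98 and a one-sided test 7.93. The figure of 60 is therefore consistent with a two-sample comparison of means with SD about 7.0. It can be neither confirmed nor refuted.

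**Step 2: cost of the rank test alone.** Under normality its efficiency relative to the t-test is 3/π = 0.955.

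- Power at 60 per group: Φ(2.802 × √0.955 − 1.960) = Φ(0.778) = 78%.
- Number needed for 80%: 60/0.955 = 62.8, so 63 per group, within the 65 recruited.

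**Step 3: effect of using baseline.** ANCOVA multiplies the standard error by √(1 − ρ²). Because the SD was solved to give 80% unadjusted, power is Φ[2.802/√(1 − ρ²) − 1.960].

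| ρ (assumed) | SE factor | Power at 60 per group | n per group for 80%: 60(1 − ρ²) | Unadjusted n equivalent to 60: 60/(1 − ρ²) |
|---|---|---|---|---|
| 0.3 | 0.954 | 83.6% | 55 | 66 |
| 0.5 | 0.866 | 89.9% | 45 | 80 |
| 0.7 | 0.714 | 97.5% | 31 | 118 |

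**Step 4: simulation check.** 4,000 trials were simulated per ρ, with integer scores held within 9–63, SD 7.04 and a true shift of 3.6.

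| ρ | Rank test, follow-up score | Rank test, change score | ANCOVA |
|---|---|---|---|
| 0.3 | 78% | 64% | 84% |
| 0.5 | 77% | 77% | 88% |
| 0.7 | 78% | 93% | 97% |

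Rank-testing change scores is not a reliable substitute: it falls below ANCOVA in every case, and at ρ = 0.3 below the plain rank test.

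**Step 5: size of a chance imbalance.** The baseline difference between groups has standard error 7.0 × √(2/60) = 1.28 points. At ρ = 0.5, an imbalance of one standard error moves the unadjusted follow-up difference by 0.5 × 1.28 = 0.64 points, which is 0.64/3.6 = 18% of the target. The unadjusted standard error already allows for this; adjustment removes it.

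**The case against.** The strongest reply is that the section is short, the full protocol and analysis plan are not shown, and listing occasions of comparison does not say that follow-up scores will be analysed without baseline. A separate plan could add it, and rank ANCOVA would be both non-parametric and baseline-adjusted, so the non-parametric sentence does not by itself rule adjustment out. This stands as a limit: the point concerns the analysis as described, for which a better method is available at almost no cost. It does not answer the wrong rationale. A parametric ANCOVA or mixed model would depart from the present text.

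Four stronger readings are tempting and are not supported.

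- *The rank test is invalid.* It is not. It is valid for scores and for counts, and type I error is unaffected. With skewed or bounded scores it may match or beat the t-test, and the protocol gives no distributions.
- *The plan cannot yield an effect in points.* A Hodges–Lehmann shift with its interval is in scale points, and descriptive means could be reported. The accurate statement is that no such estimate with a confidence interval is planned. The shift equals a mean difference only under a pure location model.
- *Chance baseline imbalance biases the result.* Under randomisation the unadjusted comparison is unbiased over repeated allocations. The loss is one of precision.
- *Baseline data are wholly unused.* The groups are compared at baseline, and the last-value rule for dropouts may carry a baseline score forward. Baseline is absent only from the effect comparison as described.

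It is also fair to say that age is only a descriptor, that visit counts serve a secondary objective, and that treating summed ratings as ordinal is a widely held, cautious position. The false premise matters mainly because it is the sole reason given for the choice of method.

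**Conclusion.** The point holds in this limited form. The justification is untrue of several recorded variables and sits badly with a sample size expressed in SDO points. The analysis as described makes no use of baseline in the follow-up comparison and plans no estimate in points with an interval.

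The choice of a rank test is the minor part, about 2 power points under normality. The unused baseline is the larger part: roughly 6, 12 and 20 power points below ANCOVA at ρ of 0.3, 0.5 and 0.7 (83.6, 89.9 and 97.5 against about 78). These sizes rest on assumed correlations, approximate normality, a two-sided test and a back-solved SD. If the true SD were 8 or 9, unadjusted power at 60 per group would be about 69% or 59%, and the gain from adjustment would matter more.

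This is an inexpensive improvement that should be made, not an error that would invalidate the trial. Separately, the 9–63 range fits nine items scored 1–7 (9 × 1 to 9 × 7), whereas the trial uses 14 items (14–98 if all are summed), so the scale to which 3.6 points refers also needs settling.

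**What to change.** - Make the main analysis of each outcome score that has a baseline value a baseline-adjusted comparison: ANCOVA, or a repeated-measures model, with arm and the baseline value of the same score. Report the adjusted mean difference in points with a 95% confidence interval.
- If an ordinal approach is kept, use rank ANCOVA or a proportional-odds model with baseline as covariate, and report an effect estimate with its confidence interval.
- Keep the unadjusted rank test as a sensitivity analysis.
- Correct the statement that all variables are nominal or ordinal. Say instead that the items are ordinal, and how the multi-item scores, the visit counts and age will be treated.

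The cost is wording in the protocol or analysis plan and some analysis work. No new data or participants are needed. The change should be fixed and dated before outcome data are compared by group.
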